## Data collection plan and management

The initial survey will be conducted within selected urban slum communities to identify individuals diagnosed with both diabetes mellitus and hypertension. Eligible participants will be approached at their households to ensure accessibility and convenience. Trained community health workers, under the supervision of the research team, will carry out the survey following standardized procedures to ensure consistency and accuracy. After screening for eligibility and obtaining written informed consent, baseline data will be collected using structured interviews. Once baseline assessments are completed, participants will be allocated to either the intervention or control group using a computer-generated block randomization procedure. Follow-up data will be collected at multiple time points: baseline, 2 months, 3 months, and 6 months to evaluate both short- and mid-term outcomes.

## Statistical analysis

Data analysis will be performed using SPSS version 28.0. Descriptive statistics, including mean, standard deviation, median, interquartile range, frequency, and percentage, will be calculated to summarize participant characteristics and outcome variables [18]. Inferential statistics, such as independent sample *t*-tests and repeated measures ANOVA, will be used to assess differences in outcomes within and between groups. The choice of parametric or non-parametric tests will depend on the distribution and normality of the data [19].

All analyses will follow the intention-to-treat principle, ensuring that each participant is analyzed in the group to which they were originally assigned, regardless of adherence to the intervention. Missing outcome data will be carefully addressed based on the nature of the missingness. For data missing at random, multiple imputation techniques will be applied. For data not missing at random, alternative approaches, such as last observation carried forward or mean imputation, will be employed. Effectiveness of the intervention will be expressed as differences in proportions with 95 % confidence intervals and 80 % statistical power. Comparisons will be made using appropriate statistical tests with adjustments for multiple comparisons

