## Limitations

This randomized controlled trial has several limitations. First, it is conducted in selected urban slums, which may limit generalizability to rural areas or populations with higher socioeconomic status. Participants’ sociodemographic profiles will be documented to provide contextual interpretation of the findings. Second, blinding is not employed, and participants are aware of their group allocation, which may introduce performance bias, particularly in self-reported outcomes. To mitigate this, validated assessment tools will be used, and data will be collected by trained personnel who are not involved in the intervention. Third, the intervention relies on participants’ attendance at yoga and counseling sessions, as well as adherence to home-based monitoring. Variations in participation may influence outcomes; therefore, reminder calls, motivational support, and flexible scheduling will be implemented to enhance adherence. Fourth, potential confounding factors such as concurrent treatments, dietary changes, or lifestyle modifications cannot be fully controlled. Baseline assessments and ongoing monitoring will help account for these factors during analysis.

Additionally, given the study’s focus on urban slum populations, access to regular healthcare and diagnostic services may be limited. This could lead to underdiagnosis or delayed identification of chronic conditions, affecting the representativeness of the recruited sample. Consequently, the findings are most generalizable to similar urban, resource-constrained communities rather than broader urban or rural populations. Nevertheless, by leveraging existing public health infrastructure, including urban primary health centers, NCD registers, and frontline health workers, the study reflects real-world conditions and aims to generate contextually relevant evidence that can inform scalable community-based interventions in comparable low-resource settings.

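### The between-group methods named make no use of baseline as a covariate, leave open which term tests the intervention, and let a normality check choose the test

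*Protocol article*

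**What the plan says.** The Data collection plan and management section sets assessments at "baseline, 2 months, 3 months, and 6 months to evaluate both short- and mid-term outcomes". The outcome subsections repeat this schedule for the clinical measures, health literacy, medication adherence and quality of life, so every outcome has a baseline value.

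For inference, the Statistical analysis section offers independent-sample t-tests and repeated measures ANOVA as examples. It says that "repeated measures ANOVA, will be used to assess differences in outcomes within and between groups" and adds: "The choice of parametric or non-parametric tests will depend on the distribution and normality of the data". It names no baseline covariate, and it does not say which ANOVA term or which visit carries the test of the intervention.

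The same section commits to analysis by randomised group: "All analyses will follow the intention-to-treat principle, ensuring that each participant is analyzed in the group to which they were originally assigned". On missing values it says "For data missing at random, multiple imputation techniques will be applied", and for data not missing at random that "alternative approaches, such as last observation carried forward or mean imputation, will be employed".

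The Limitations section, after listing possible confounders such as concurrent treatment, says: "Baseline assessments and ongoing monitoring will help account for these factors during analysis". No model is attached to that sentence.

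**The concern.** There are three difficulties with the methods as named.

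- An independent t-test on a follow-up value ignores the participant's own baseline, which is usually the strongest available predictor of that value.
- Repeated measures ANOVA on the four-visit series can treat baseline as an outcome. Its group main effect then averages in a visit that precedes allocation, where no effect can exist. Its group-by-time interaction avoids this, but as an omnibus test it yields no treatment difference at a given visit. The article does not say which term is meant.
- Choosing between a parametric and a rank-based test after looking at the distribution leaves the test, and with it the quantity estimated, open until outcome data have been seen.

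At stake are precision that costs nothing to obtain, and a treatment effect whose definition could depend on which output is read.

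**Working it through.** **Inputs.** From the Sample size section: SD 0.74 (the symbol is a variance, but the text describes a standard deviation), difference 0.40, z-values 1.96 and 0.84, attrition 10%. The article gives no baseline-outcome correlation r, so 0.3, 0.5 and 0.7 are assumed.

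**The plan's own figure.** n = 2 × 0.74² × (1.96 + 0.84)² / 0.40² = 2 × 0.5476 × 7.84 / 0.16 = 53.66, so 54 per arm; 54 / 0.9 = 60. Both stated figures reproduce, and they rest on an unadjusted comparison of two means.

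**Unadjusted t-test at one visit, 54 per arm** (normal approximation). Signal = (0.40 / 0.74) × √(54/2) = 0.5405 × 5.196 = 2.809. Power = Φ(2.809 − 1.96) = Φ(0.849) = 80.2%.

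**Baseline-adjusted comparison at one visit.** The SD shrinks by √(1 − r²), so the signal is 2.809 / √(1 − r²).

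- r = 0.3: 2.809 / 0.954 = 2.944, power 83.8%
- r = 0.5: 2.809 / 0.866 = 3.243, power 90.0%
- r = 0.7: 2.809 / 0.714 = 3.933, power 97.6%

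Equivalently, 80% power would need 49, 41 or 28 per arm instead of 54.

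**ANOVA group main effect with baseline as one of four levels.** Assume compound symmetry and a constant effect at all three follow-ups. The estimated effect is (0 + 0.40 + 0.40 + 0.40) / 4 = 0.30. The variance of a participant's four-visit mean is SD² × (1 + 3r) / 4, so the signal is 0.75 × 2.809 / √((1 + 3r)/4).

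- r = 0.3: 2.107 / 0.689 = 3.057, power 86.4%
- r = 0.5: 2.107 / 0.791 = 2.665, power 75.9%
- r = 0.7: 2.107 / 0.880 = 2.393, power 66.7%

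**Group-by-time type contrast** (mean of the three follow-ups minus baseline). The effect remains 0.40, with variance SD² × [(1 + 2r)/3 + 1 − 2r]. Power is 82.8%, 93.1% and 99.3%. This is a single-degree-of-freedom contrast. The omnibus interaction has three degrees of freedom, and its power was not computed.

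| Analysis | r = 0.3 | r = 0.5 | r = 0.7 |
|---|---|---|---|
| t-test, one visit | 80.2% | 80.2% | 80.2% |
| Baseline-adjusted, one visit | 83.8% | 90.0% | 97.6% |
| ANOVA group main effect, baseline as a level | 86.4% | 75.9% | 66.7% |
| Follow-up mean minus baseline | 82.8% | 93.1% | 99.3% |

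The rows do not all target the same quantity: the first two concern one visit, the last two an average over visits.

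**The case against.** The article condenses a fuller plan, introduces its methods as examples, and mentions using baseline assessments in the analysis. It nowhere says that analyses will be unadjusted. This has some force, and the point should not be read as saying that adjustment has been ruled out. But the article chose to name its between-group methods and neither is baseline-adjusted. The Limitations sentence is about confounders and supplies no model. The normality rule is explicit text, not silence.

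The lack of adjustment also causes no bias in a randomised comparison and does not undermine the sample size. That stands in full: the loss is one of efficiency and clarity. Likewise, the named t-tests do give a difference at each visit, so visit-specific estimates are not out of reach.

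The dilution is conditional. It affects the group main effect only, and only if baseline is one of the levels. At a correlation of 0.3 that test still has 86.4% power, above the planned 80% and above single-visit adjustment, because it averages several visits.

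A reader might infer that, because classical repeated measures ANOVA needs complete series, participants who miss a visit will be dropped and intention-to-treat broken. The documents do not support this. The same section plans imputation for data missing at random and for data not missing at random, and no sentence excludes incomplete participants. A reader might also set the diluted main effect against a baseline-adjusted mean of all three follow-ups. That would overstate the gain, because the primary result recommended here is a difference at one visit.

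**Conclusion.** The concern holds as a matter of efficiency and specification, not validity; the change should be made but is not essential to a sound trial. The unadjusted t-test delivers the planned power, and baseline adjustment at one visit would add roughly 4, 10 or 17 percentage points (83.8, 90.0 or 97.6 minus 80.2) at correlations of 0.3, 0.5 or 0.7. Reading the ANOVA group main effect with baseline as a level would understate a constant effect by a quarter whatever the correlation. Its power would fall below 80% at 0.5 and 0.7, but not at 0.3. These figures rest on assumed correlations and 54 per arm. Those for the ANOVA terms also assume compound symmetry and a constant effect after baseline. Choosing the test by a normality check is a separate weakness and depends on none of these assumptions.

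**What to change.** Name one baseline-adjusted primary analysis. Either of these would serve:

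- ANCOVA at the primary visit, with the baseline value as covariate; or
- a linear mixed model on the 2-, 3- and 6-month values with arm, visit, arm-by-visit, baseline and baseline-by-visit.

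Name the visit at which the treatment effect is judged and report the adjusted mean difference there with its 95% CI. Keep this model as primary whatever a normality test shows, with rank-based or robust analyses as sensitivity only. State in one sentence how the planned imputation feeds the chosen model. The cost is a change of wording in the analysis section: the baseline data are already being collected, and neither the sample size nor the visit schedule changes.

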## Sample size

The sample size was calculated using the formula:$$N=\frac{2\sigma^{2}{\left(Z_{1-\alpha /2}+Z_{1-\beta }\right)}^{2}}{\delta^{2}}$$

Where:*N* = required sample size per groupσ² = pooled standard deviation of the primary outcome measure (assumed as 0.74 from prior studies)δ² = Anticipated difference in mean outcomes between groups (0.40)Z_1−α/2_ = standard normal variate corresponding to a 95 % confidence level (1.96)Z_1−β_ = standard normal variate corresponding to 80 % power (0.84)

By applying these values, the estimated sample size is approximately 54 participants per group. Considering a 10 % attrition rate, the final sample size will be 120 participants (60 in the intervention group and 60 in the control group).

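### Outcome data judged not missing at random are to be filled by last observation carried forward or mean imputation, neither of which models that kind of missingness

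*Protocol article*

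**What the plan says.** The rule is in the Statistical analysis section of the protocol article. It opens with the principle "Missing outcome data will be carefully addressed based on the nature of the missingness". Two branches follow. The first is "For data missing at random, multiple imputation techniques will be applied". The second is "For data not missing at random, alternative approaches, such as last observation carried forward or mean imputation, will be employed". The completed data then go into the planned tests: "Inferential statistics, such as independent sample *t*-tests and repeated measures ANOVA, will be used to assess differences in outcomes within and between groups".

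No other section limits or corrects the second branch. Outcomes are measured at baseline and at 2, 3 and 6 months (Data collection plan and management). The intervention lasts 6 weeks (Intervention group), and the sample size allows for 10% attrition (Sample size).

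**The concern.** There are two faults.

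- **The branching rule cannot be carried out.** Whether missingness depends on the unseen value, given what was observed, cannot be read from the observed data. Sorting the data into the two branches is therefore a judgement. In a trial without blinding (Limitations), it leaves the choice of method open after the data are seen.
- **The methods in the second branch do not fit it.** Data are not missing at random when missingness depends on the unseen value. Mean imputation supposes that the missing values sit at the average of the observed ones. LOCF supposes no change after the last visit attended. Neither represents the dependence that defines this branch. The plan thus keeps its better method for the easier case and uses single imputation for the harder one.

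At stake are bias in the between-group difference and, for one version of mean imputation, a test that rejects too often.

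**Working it through.** **Inputs.** From the Sample size section: "pooled standard deviation of the primary outcome measure (assumed as 0.74 from prior studies", 0.74; "Anticipated difference in mean outcomes between groups (0.40", 0.40; z values 1.96 and 0.84; 10% attrition; 60 per arm.

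**The plan's own figure.** n = 2 × 0.74² × (1.96 + 0.84)² / 0.40² = 53.66, so 54 per arm; 54 / 0.90 = 60. This reproduces. It does so only with 0.74 as the standard deviation and 0.40 as the difference, although the legend attaches them to σ² and δ². They are used that way below.

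**Mean imputation with arm means.** Let N = 60 and n_obs = the number observed per arm, with missingness unrelated to outcome.

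- Reported SE = 0.74 × √((n_obs − 1)/(N − 1)) × √(2/N)
- True SE = 0.74 × √(2/n_obs)
- Type I error = 2 × (1 − Φ(1.96 × ratio))

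At 10% missing, n_obs = 54. The filled-in SD is 0.74 × √(53/59) = 0.7014, the reported SE is 0.7014 × √(2/60) = 0.128, and the true SE is 0.74 × √(2/54) = 0.142.

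| Share filled | SE ratio | Type I error |
|---|---|---|
| 5% (assumed) | 0.95 | 6.3% |
| 10% (plan's attrition) | 0.90 | 7.8% |
| 20% (assumed) | 0.80 | 11.8% |

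The ratio is close to 1 − m, where m is the share filled. That shortcut gives 11.7% at 20%. A simulation of 20,000 runs gave 7.8% at 10% and 11.9% at 20%.

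**Mean imputation with the overall mean.** Each arm mean becomes (1 − m) × arm mean + m × overall mean, so the difference is multiplied by (1 − m): 0.90 × 0.40 = 0.36 and 0.80 × 0.40 = 0.32. The sampling variance of that shrunken difference is (1 − m)² × 2σ²/((1 − m)N) = (1 − m) × 2σ²/N, which is about what the t-test reports. Type I error therefore stays near 5% (simulated: 4.9% at 10%, 5.3% at 20%). The fault here is dilution of a real effect.

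**Bias under informative dropout.** This was simulated with 4,000 runs per scenario, 60 per arm and SD 0.74. The within-person correlation of 0.6 and the logistic dropout on the 6-month value are assumptions, not figures from the document. Dropouts had attended through 3 months, so LOCF carried the 3-month value. In the two unequal scenarios there was no true effect.

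| Scenario (missing: control, intervention) | Mean imputation (arm means): bias, 95% coverage | LOCF: bias, 95% coverage |
|---|---|---|
| Value-dependent in intervention arm only (14%, 19%) | −0.136, 77% | −0.042, 94% |
| Value-dependent in both arms, unequal rates (6%, 19%) | −0.091, 85% | −0.026, 94% |
| Value-dependent in both arms, equal rates (about 10% each), true effect −0.40 | 0.001, 91% | 0.011, 95% |

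Mean imputation had exactly the bias of the complete cases in every row, so it removes none. The largest value is 0.136/0.40 = 0.34 of the planned difference. The bias is negligible when dropout works alike in both arms.

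**LOCF, direction and standard error.** The bias at 6 months is the share filled times the gap between the carried value and the unseen 6-month value, compared between arms. As an illustration, suppose control dropouts do not change on average and 10% of the intervention arm is filled.

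- If they carry a 2-month gain of 0.40 that is wholly lost by 6 months, the bias is 0.10 × 0.40 = 0.04 in favour of the intervention.
- If they carry baseline although they would have gained 0.40, it is 0.04 towards no effect.

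In the simulations, the LOCF standard error in a per-visit t-test was 0.99 to 1.02 of its own sampling variation. Repeated measures ANOVA was not examined.

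**The case against.** A reader might infer that both methods make standard errors too small, that the trial's type I error is inflated, and that the result is tilted towards the intervention. The documents do not support that.

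- **Which mean.** The article does not say whether the arm mean or the overall mean is meant. Only the arm mean inflates type I error; the overall mean works against the intervention.
- **How much is filled.** The 7.8% needs the whole 10% attrition to be judged not missing at random and then mean-imputed. Part would go to multiple imputation or LOCF, and home visits and reminders are planned to limit loss (Follow-up and data collection procedures).
- **LOCF.** In a per-visit t-test its standard error tracked its sampling variation. A tilt towards the intervention needs dropouts who attended at 2 months, had improved, and then relapsed. Nurse contact continues every two weeks after the first month, and community health workers encourage continued practice, so relapse is not a given. Those lost before 2 months carry baseline forward.
- **Condensed article.** The two methods are introduced as examples, and a full analysis plan may say more. Detail such as a delta range may properly sit there.

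The first three objections stand and limit the size and direction of the problem. The last stands only in part. The two methods are the only ones named for this branch, and the sentence commits to using approaches of that kind. That is a stated choice, not a missing detail.

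**Conclusion.** The rule is wrong as written and should be fixed. It rests on a distinction that the data cannot make, and for data not missing at random it names two methods that do not address that mechanism.

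The size is moderate and conditional. Type I error is about 7.8% if arm means are used and all of the 10% attrition is filled so, about 6.3% if 5% is, and just under 12% at an assumed 20%. With the overall mean there is no inflation, but 0.40 is diluted to about 0.36 at 10% missing. Bias from dropout that differs between arms passes through mean imputation unchanged; its size rests on the assumed dropout models. LOCF may bias the 6-month comparison in either direction, and too small a standard error has not been shown for it.

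**What to change.** In the Statistical analysis section:

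1. Delete LOCF and mean imputation, and drop the choice of method by judged mechanism.
2. State one primary analysis under missing at random for all randomised participants: a likelihood-based mixed model over the visits, or multiple imputation by arm using baseline and interim visits.
3. Examine departures from missing at random as a sensitivity analysis, by delta-adjusted or reference-based multiple imputation over a stated range, and report the tipping point at which the conclusion changes.

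The cost is a change of wording, a few extra analysis runs and slightly wider intervals. The sample size of 60 per arm and the visit schedule are unaffected.

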### Clinical outcome

Clinical outcomes will include blood pressure and blood sugar levels. Blood pressure will be measured using a calibrated digital sphygmomanometer, with two readings taken and averaged to ensure accuracy. Blood glucose levels will be measured through random blood sugar test using a standardized glucometer. These measurements will be collected at baseline, 2 months, 3 months, and 6 months to track changes over time.

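### The stated effect measure (difference in proportions, with 80% power attached) contradicts the sample size, the named tests and the outcomes, which all concern means of levels or scores

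*Protocol article*

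**What the plan says.** The Statistical analysis section of the protocol article first names the tests: "Inferential statistics, such as independent sample *t*-tests and repeated measures ANOVA, will be used to assess differences in outcomes within and between groups". Non-parametric tests may be substituted, depending on the distribution of the data. The next paragraph then fixes how the result is to be reported: "Effectiveness of the intervention will be expressed as differences in proportions", with 95% confidence intervals and 80% power attached in the same sentence.

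The Sample size section uses the two-means formula. Its effect is the "Anticipated difference in mean outcomes between groups (0.40"), and its spread is the "pooled standard deviation of the primary outcome measure (assumed as 0.74 from prior studies"). The power enters there as the "standard normal variate corresponding to 80 % power (0.84").

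On the outcomes, the Clinical outcome section states: "Clinical outcomes will include blood pressure and blood sugar levels". The next three sections describe a 14-item health literacy scale, the 8-item adherence scale and a 16-item quality-of-life questionnaire. None of these sections turns its outcome into a yes/no endpoint. The Background gives 140/90 mmHg, but only to define hypertension. The Aim of the study speaks of blood pressure and blood sugar control without making control a binary outcome.

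**The concern.** One sentence governs how the effect of the intervention is expressed, and it sits on a different scale from the rest of the design. Read literally, the test would compare means while the reported effect and its interval would compare proportions. The two can disagree: a clear difference in means can sit beside an interval for a proportion that includes zero, or the reverse, depending on the cut-off.

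The same sentence attaches 80% power to the reported effect. Power is a property of the design under an assumed effect, not part of an estimate. The only power calculation in the article is for means, so the figure does not carry over to a proportion.

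**Working it through.** **1. Reproduce the plan's own figure.** Inputs from Sample size: difference 0.40, SD 0.74, Z values 1.96 and 0.84.

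n per group = 2 × 0.74² × (1.96 + 0.84)² / 0.40² = 53.7, rounded up to 54. With 10% attrition, 54 / 0.90 = 60 per group, 120 in total. Both stated figures reproduce.

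The article labels 0.74 as σ² and 0.40 as δ². Using 0.74 as a variance gives 2 × 0.74 × 2.8² / 0.40² = 72.5, which does not match, so 0.74 was used as the SD and 0.40 as the difference.

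**2. Power for the measure that was sized.** Standard error of the difference in means = 0.74 × √(2/54) = 0.1424. Power = Φ(0.40/0.1424 − 1.96) = Φ(0.849) = 80.2%. The 80% belongs here.

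**3. Power if the same outcome is split and the proportion decides.** The article gives no cut-off and no expected proportion, so the following are assumptions: a normal outcome, equal SDs in both groups, a pure shift of 0.40/0.74 = 0.54 SD, and a cut-off placed c SD from the midpoint of the two group means. Sample size does not say which outcome 0.40 and 0.74 describe, so applying 0.54 SD to any particular outcome is also an assumption.

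Proportions above the cut-off: p1 = Φ(0.27 − c) and p0 = Φ(−0.27 − c). With n = 54, the unpooled standard error is √[(p1(1 − p1) + p0(1 − p0))/n]. Power is Φ(difference/SE − 1.96) with the unpooled variance throughout, and slightly lower if the null variance is pooled.

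| Cut-off | p1 vs p0 | Difference | Power, unpooled | Power, pooled null |
|---|---|---|---|---|
| centre (c = 0) | 60.7% vs 39.3% | 21.3 points | 62% | 60% |
| 0.5 SD off | 40.9% vs 22.1% | 18.9 points | 58% | 56% |
| 1 SD off | 23.3% vs 10.2% | 13.1 points | 46% | 44% |

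For the central split, 0.213 / 0.0940 − 1.96 = 0.306, and Φ(0.306) = 62%. By symmetry, a cut-off the same distance on the other side gives the same power. If all 60 per group were evaluable, the central split would reach about 65–67%.

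**4. Size needed for 80% at the central split.** Unpooled: 2.8² × (2 × 0.607 × 0.393) / 0.213² = 82.4 before rounding of inputs, so 83 per group. With the null variance pooled: 86 per group. The plan has 54.

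**5. Difference in proportions that 54 per group can detect.** With the pooled null variance, 80% power needs about 25 points if the control proportion is 20%, and about 26 to 27 points for control proportions of 30% to 50%. Under the assumptions in step 3, the planned shift yields at most about 21 points.

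**The case against.** The strongest reply is that the tests of means remain in the plan. The proportions sentence concerns how effectiveness is expressed, not which test decides. A reader might infer that the main result will therefore lack the planned power, but the documents do not support that: if the t-test or repeated measures ANOVA decides, the planned 80% stands. This part of the reply holds, and the power loss is conditional.

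A second reply is that cut-offs may be set in a statistical analysis plan that is not shown, and that some categorical reporting is plausible because percentages are listed among the descriptive summaries and the aim speaks of control. That also holds. The absence of cut-offs from a condensed article is not an error in itself. A reader might go on to infer that cut-offs will be picked after the data are seen; nothing in the article says so.

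A third reply is that a binary endpoint could show a larger effect than a split of the planned shift implies. At roughly 25 points or more, 54 per group would still give 80%. That is possible, but the article states no such expectation.

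None of this reconciles the sentence with the Sample size section. A cut-off defined elsewhere would not make a calculation for means support 80% power for a proportion.

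**Conclusion.** The contradiction is established from the text alone: the effect measure is a difference in proportions, while the sizing, the named tests and the outcome descriptions concern means of levels or scores. The 80% power applies to the comparison of means only, and attaching it to the reported effect is wrong.

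The numerical loss is conditional. It arises only if the proportion is the deciding analysis, and its size rests on the assumptions listed in the working. On those terms, power falls from 80% to about 60–62% at best, and the requirement rises from 54 to about 83–86 per group. The width of each range reflects only the choice of variance formula. Different outcome distributions or larger true differences would change these figures, but not the contradiction.

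**What to change.** Replace the sentence in Statistical analysis so that effectiveness is the between-group difference in means (intervention minus control) with its 95% confidence interval, as in Sample size. Adjusting that difference for the baseline value, which is already collected, is an option that costs nothing, but the repair does not depend on it.

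If proportions are wanted, for example those with blood pressure or glucose under control, list them as secondary, with the cut-offs fixed before analysis. Delete the reference to 80% power.

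The cost is one sentence of wording, and the 120 participants stand. The alternative, keeping the proportion as the measure of effectiveness, would need a defined binary endpoint, an expected control proportion and a new sample size calculation.
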